## Abstract

**Background:**

Many adults are insufficiently physically active, have prolonged sedentary behaviour and report poor sleep. These behaviours can be improved by interventions that include education, goal setting, self-monitoring, and feedback strategies. Few interventions have explicitly targeted these behaviours simultaneously or examined the relative efficacy of different self-monitoring methods.

**Methods/Design:**

This study aims to compare the efficacy of two self-monitoring methods in an app-based multi-behaviour intervention to improve objectively measured physical activity, sedentary, and sleep behaviours, in a 9 week 2–arm randomised trial. Participants will be adults (*n* = 64) who report being physically inactive, sitting >8 h/day and frequent insufficient sleep (≥14 days out of last 30). The “*Balanced*” intervention is delivered via a smartphone ‘app’, and includes education materials (guidelines, strategies to promote change in behaviour), goal setting, self-monitoring and feedback support. Participants will be randomly allocated to either a device-entered or user-entered self-monitoring method. The device-entered group will be provided with a activity tracker to self-monitor behaviours. The user-entered group will recall and manually record behaviours. Assessments will be conducted at 0, 3, 6, and 9 weeks. Physical activity, sedentary behaviour and sleep-wake behaviours will be measured using the wrist worn Geneactiv accelerometer. Linear mixed models will be used to examine differences between groups and over time using an alpha of 0.01.

**Discussion:**

This study will evaluate an app-based multi-behavioural intervention to improve physical activity, sedentary behaviour and sleep; and the relative efficacy of two different approaches to self-monitoring these behaviours. Outcomes will provide information to inform future interventions and self-monitoring targeting these behaviours.

**Trial registration:**

ACTRN12615000182594 (Australian New Zealand Clinical Trials Registry. Registry URL: www.anzctr.org.au; registered prospectively on 25 February 2015).

## Background

Physical activity and sleep are important for the promotion of health and well-being [1–3]. Insufficient moderate-to-vigorous intensity physical activity, prolonged sedentary behaviour, and poor sleep behaviours - sleeping either too few/many hours or having poor quality sleep – increase the risk of cardiovascular disease (CVD), type 2 diabetes, poor quality of life, anxiety, depressive symptoms, and all-cause mortality [2–7]. Internationally, considerable proportions of the adult population report engaging in one or more of these health compromising behaviours [8–13].

Although multi-behaviour change interventions are frequently conducted, few explicitly target improvements in physical activity, sedentary and sleep behaviours [14–16]. There is good rationale to target these behaviours simultaneously, as they are thought to share a reciprocal relationship. Greater activity levels are thought to improve sleep quality, and better sleep quality can contribute to higher levels of moderate-to-vigorous intensity physical activity and total daily activity [17–20]. In addition, these reciprocal relationships may be enhanced through co-action - a mechanism in multi-behaviour change interventions where change in one behaviour can lead to change, either intentionally or unintentionally, in subsequent behaviours [21]. To maximise change in multi-behaviour interventions it is necessary to provide participants with dedicated behaviour change techniques specific to the targeted behaviours such as goal setting, self-monitoring, and feedback on performance [22–24]. There is substantial evidence that self-monitoring improves a number of health behaviours [25, 26]. Self-monitoring involves individuals tracking behaviour, evaluating progress towards a pre-determined standard, and being aware of the factors that inhibit or facilitate progress [23, 24, 27]. Physical activity, sedentary and sleep behaviours can be manually self-monitored by individuals recalling key aspects of the behaviour (e.g., duration of activity or sleep, time to sleep, time to wake) and recording this information into a paper or electronic diary [28–32]. However, this is vulnerable to social desirability and recall bias, and can have high participant burden [33]. Previous interventions have included devices such as pedometers to partially overcome these limitations by asking participants to enter pedometer steps into the intervention platform [33]. Self-monitoring can also now be automated. This can be achieved by using newly available activity trackers (eg. Fitbit) that also allow physical activity, sedentary and sleep behaviours to be self-monitored and automatically synchronised to mobile devices, which can display feedback on behaviour [25, 34]. However, these devices may increase costs of intervention, present additional technical barriers (e.g. synchronising data across multiple platforms) and the also lower some of the cognitive processing associated self-monitoring which is a key part of self-monitoring [27]. The impact of this on the efficacy of self-monitoring interventions is unknown.

Technology-based interventions such as those delivered by websites and smartphone applications ‘apps’ are increasingly used due to the large potential reach they offer, increased access, including the ability to overcome the need to attend face to face sessions to receive the intervention [35–37]. Technology-based interventions can integrate key behaviour strategies, including self-monitoring and feedback, and to date have been successful in improving a variety of health behaviours over shorter time periods (<12 weeks) [26, 36, 37]. Participant usage of and engagement with the intervention platform is frequently examined and appears to be related to intervention efficacy [26, 36, 38]. Though many technology-based interventions observe large declines in usage and engagement during the first four weeks of the intervention period and do not assess behaviour until much later (e.g., week 12) [28, 38, 39]. Examining behaviour change during time periods when usage and engagement frequently declines may provide greater insight on this relationship and improve subsequent interventions.

The primary aim of this study is to compare the efficacy of device-entered and user-entered self-monitoring methods in a app-based multi-behaviour intervention to improve objectively measured physical activity, sedentary, and sleep behaviours, in a 9 week 2-arm randomised trial. Secondary outcomes will include self-reported physical activity, sitting time, sleep quality, sleep hygiene, anxiety, depression, stress, quality of life and cardiometabolic risk. Potential mediators include psychosocial correlates of behaviours and intervention usage and engagement. Process measures will be collected at the conclusion of the 9 week intervention period and will include reasons for participating in the study, expectations of the study, perceived aesthetics, functionality and appropriateness of the intervention platform, and suggested modifications to the intervention.

## Methods

### Trial design

The Balanced study is a two-arm randomised trial over 9 weeks. The intervention groups are:*Balanced* intervention with device-entered self-monitoring method,*Balanced* intervention with user-entered self-monitoring method.

All participants will have access to the same smartphone-based *Balanced* intervention only the method of self-monitoring is different. Participants in the device-entered self-monitoring group will be provided with a wrist-worn activity tracker to automatically measure and upload physical activity, sedentary and sleep behaviour data. Participants in the user-entered self-monitoring group will recall and manually enter information on physical activity, sedentary and sleep behaviours. Participants will complete assessments at 0, 3, 6, and 9 weeks (Fig. 1). The study received approval from the Human Research Ethics Committee of The University of Newcastle, Australia (Reference Number H-2014-0336) and is registered with the Australian and New Zealand Clinical Trials Registry (ACTRN12615000182594). All participants provided informed consent to participate and could withdraw at any time for any reason. The funding body had no role in the design, conduct or reporting of the trial.

**Fig. 1 Fig1:**
[figure not shown]
Study Design

### Participant recruitment

Sixty-four participants will be recruited from the Newcastle area, New South Wales, Australia using posters distributed at The University of Newcastle Callaghan campus, local businesses, community notice boards (both physical and electronically), community events; and study advertisements via radio, electronic communication (email lists, social media), and participant registries. Recruitment commenced in July 2015. Individuals interested in participating in the trial will be directed to an online screening survey to assess eligibility. Those who meet the inclusion criteria will be contacted by project staff via phone or email to arrange an appointment time. Ineligible participants will be contacted via phone or email to advise them they are ineligible and offered access to the Balanced app.

### Eligibility

To be eligible for inclusion into the study, individuals must report:Being aged between 18 and 55 years,Weight and height consistent with a Body Mass Index (BMI) between 18.5 and 35.0,Engaging in less than 30 min of moderate to vigorous intensity physical activity on 5 days per week which is comparable with recommendations [40],Spending at least 8 h per day sitting on 5 or more days per week, which is comparable with research identifying risk levels of mortality and chronic disease above this level [41, 42],Waking up feeling like they needed more rest/sleep on 14 or more days per month, which is comparable with research identifying higher risk of chronic disease above this level [4],Absence of any condition that makes it unsafe for them to change their activity, sitting and sleep behaviours,Absence of an existing sleep disorder such as insomnia, sleep apnoea, restless legs syndrome,Not being employed in shift work,Not taking any medications to induce sleep, Not travelling to any destination requiring a change in time zone of more than 3 h during the intervention period. Not currently using an app or activity tracker to track physical activity, sedentary or sleep behaviours. Having access to either an Android or iOS smartphone or tablet with access to the internet.

### Study procedure

Eligible participants will be asked to attend the University of Newcastle on eight occasions to complete four assessments (2 visits required per assessment). Table 1 provides an overview of the assessments conducted at each visit. Visits 3, 5 and 7 occur 3, 6 and 9 weeks after visit 2. At visits 1, 3, 5, and 7 participants will be provided with an accelerometer to wear continuously for 7 days and return the accelerometer 8 days later visits 2, 4, 6 and 8 respectively, no other assessments occur at visits 1, 3, 5 and 7.

**Table 1 Tab1:** Overview of measurement tools, and timing of measurements

Outcome	Measure	Assessment point (Visit)
Primary Outcomes		
Objectively Measured Physical Activity, Sedentary Behaviour, Sleep^a^	Geneactiv Accelerometer	2, 4, 6, 8
Secondary Outcomes		
Self-Reported Physical Activity, Sitting Time, Sleep Quality, Sleep Timing	Active Australia Survey [66–68]	2, 4, 6, 8
	Workforce Sitting Questionnaire [69]	2, 4, 6, 8
	Pittsburgh Sleep Quality Index [70]	2, 4, 6, 8
	Sleep Timing Questionnaire [72]	2, 4, 6, 8
	Behavioral Risk Factor Surveillance Sleep Module [71]	2, 4, 6, 8
*Depression, Anxiety and Stress*	Depression, Anxiety and Stress Scale [73, 74]	2, 4, 6, 8
*Health related quality of life*	Centres for Disease Control Healthy Days Instrument [78–80].	2, 8
Mediators		
*Lifestyle Behaviour Habit*	Automaticity subscale of self-report behavioural automaticity index (Physical Activity) [81]	2, 4, 6, 8
	Automaticity subscale of self-report behavioural automaticity index (Sitting) [81]	2, 4, 6, 8
	Automaticity subscale of self-report behavioural automaticity index (Sleep) [81]	2, 4, 6, 8
Sleep Hygiene	Sleep Hygiene Index [82]	2, 4, 6, 8
*Social Cognitive Factors*	Social Cognitive Factors (Physical Activity)	2, 4, 6, 8
	Social Cognitive Factors (Sitting)	2, 4, 6, 8
	Social Cognitive Factors (Sleep)	2, 4, 6, 8
*Usability, Satisfaction*	System Usability Scale [84]	8
	Satisfaction. Newly developed items	8
Process Evaluation	Semi-Structured Interview	8
Engagement and Usage	App database	Continuous
Demographics	Commonly used items	2
Presenteeism	World Health Organization Health and Work Performance Questionnaire [85, 86]	2, 8
Anthropometrics and Blood Pressure	Standard Protocols for Height, Weight, Waist Circumference, Blood Pressure [87]	2, 4, 6, 8
Cardiometabolic Risk	Cardiochek PA measures of total cholesterol, HDL cholesterol, LDL cholesterol, triglycerides and glucose	2, 8

^a^The Geneactiv is provided to participants to begin wearing at visit 1, 3, 5, and 7 respectively

The research assistant performing height, weight, waist circumference and blood pressure measures received training to perform these measures and will be blinded to participant group allocation. Participants will also be provided with a gift voucher to the value of $10 at the completion of each of assessments in visits 2, 4, 6, and 8. Following completion of measurements during visit 2 participants will be randomised to one of the intervention groups and provided with access to the *“Balanced”* app; participants allocated to the Device-entered self-monitoring group will be provided with a Fitbit (Charge HR) activity tracker.

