### Socio-demographics, Anthropometrics and cardiometabolic risk

Participants will provide information on their age, gender, years of education, occupational level, hours of work (daytime, night time, afternoon), number of days worked in previous week and average hours of work each day. Presenteeism at work over the previous 28 days will be assessed using a single item from the World Health Organization Health and Work Performance Questionnaire [85, 86]. This item asks participants to rate their performance at work on a scale of 0 to 10, where zero is the worst performance.

A research assistant blinded to group allocation will measure height, weight, waist circumference, and blood pressure with participants dressed in light clothing and without shoes. Weight (kg) will be measured on a calibrated digital scale to 0.01 kg (Biospace BSM370 Portable Automatic BMI Stadiometer, Biospace CO, Ltd., Seoul Korea). Weight will be measured twice if the two values are within 0.1 kg. If measurements vary by more than 0.1 kg a third measurement will be taken and the average of the two measures that are within 0.1 kg will be recorded. Height (cm) will be measured to 0.1 cm using a stadiometer (Biospace BSM370 Portable Automatic BMI Stadiometer, Biospace CO, Ltd., Seoul, Korea). Two measures of height will be taken and if values are not within 0.3 cm a third measure will be taken. The average of the two height measures within 0.3 cm will be taken. Waist circumference (cm) will be measured at the umbilicus (Seca 203, Seca Gmph & Co. Hamburg, Germany). Two measures will be taken, if these measures are not within 0.5 cm a third measure of waist circumference will be taken. The average of the two waist circumference measures within 0.5 cm will be taken [87].

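### Assessor blinding is stated without qualification, but a wrist tracker issued only to the device arm would probably reveal allocation if worn to visits 4, 6 or 8, chiefly a concern for waist circumference

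*Protocol article*

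**What the plan says.** The blinding claim is made twice. Under Study procedure, the research assistant taking height, weight, waist and blood pressure "will be blinded to participant group allocation". Under Socio-demographics, Anthropometrics and cardiometabolic risk it appears again: "A research assistant blinded to group allocation will measure height, weight, waist circumference, and blood pressure". Neither statement is limited to particular visits.

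The arms differ in a physical object. Under Trial design, the device-entered group "will be provided with a wrist-worn activity tracker to automatically measure and upload physical activity, sedentary and sleep behaviour data". Study procedure gives the order of events: "Following completion of measurements during visit 2 participants will be randomised to one of the intervention groups", and at that point "participants allocated to the Device-entered self-monitoring group will be provided with a Fitbit (Charge HR) activity tracker". The user-entered group receives no tracker. Table 1 schedules anthropometry and blood pressure at visits 2, 4, 6 and 8.

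**The concern.** Blinding of an assessor can fail by two routes: the assessor learns the allocation from the list, or from the participant. The article deals with the first. The second is open by design, because what distinguishes the arms is something worn on the wrist, and the assessor handles the participant at close range to measure the waist and take blood pressure.

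An assessor who knows the arm can, without intending to, place or tension a tape differently in one arm. That would produce a between-group difference unrelated to the intervention, in data that the trial report would describe as collected blind. A reader appraising the report would have no means of seeing the problem.

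**Working it through.** No figure in the article depends on this point, so there is nothing to recompute. The check sets the relevant statements side by side.

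1. **Which assessments are exposed.** Visit 2 measurements come before randomisation and device issue (Study procedure), so they cannot be affected. Visits 4, 6 and 8 come after. That is three of the four scheduled assessments of these measures (Table 1).

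2. **Is the tracker likely to be in use then?** The tracker supplies activity, sedentary and sleep data (Device-entered self-monitoring), so its intended use covers day and night. The app was presented as a daily monitoring tool and stays available during assessment periods (Intervention). Wear at the visits is therefore plausible. It is nowhere stated.

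3. **Would a visible tracker identify the arm?** Current users of activity trackers are excluded (Eligibility), and the user-entered arm is given none. A tracker on the wrist would thus point strongly to the device arm. Participants in both arms also wear the Geneactiv on the wrist for the 7 days of each assessment (Outcome measures), but that is common to the arms and does not mask an additional device found in only one of them.

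4. **Does a stated safeguard cover this?** Under Randomisation, the sequence is generated by someone outside the assessments, kept on a database the assessors cannot reach, and concealed in opaque envelopes. These steps protect the list. They do nothing about a device in view.

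5. **Which measures can the assessor influence?**
   - *Weight*: read from a calibrated digital scale. Little room.
   - *Blood pressure and heart rate*: read from a digital sphygmomanometer. Little room.
   - *Waist*: measured by hand at the umbilicus. Placement and tension depend on the assessor. This is the measure mainly at issue.

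6. **What do the repeat rules do?** They use numeric triggers: 0.1 kg for weight, 0.3 cm for height, 0.5 cm for waist; and 10 mm Hg systolic, 5 mm Hg diastolic and 5 bpm for blood pressure and heart rate. They check agreement among readings within one visit. A consistent shift moves every waist reading together and passes at any size, so the 0.5 cm tolerance neither bounds nor estimates a bias. Some choice remains where two pairs both agree. As an illustration with assumed readings of 90.0, 90.6 and 90.3 cm: the first two differ by 0.6 cm, which triggers the third; the third is 0.3 cm from each; the two admissible averages are (90.0 + 90.3)/2 = 90.15 cm and (90.6 + 90.3)/2 = 90.45 cm. The text does not say which to use. This is a small residual choice in an otherwise fixed rule.

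7. **Are the primary outcomes touched?** All five are derived from the Geneactiv accelerometer (Outcome measures; Analysis), not from this assessor's readings. They are unaffected.

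**The case against.** The strongest reply has four parts.

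- *The article does not say the tracker is worn at the visits.* Correct. App use was left to the participant's preference, with no prompts. A reader might infer from the design that device-arm participants attend visits 4, 6 and 8 wearing the tracker, and hence that the measures are not assessed blind. The documents do not support that as fact. What stands is conditional: any participant who does attend wearing it is probably identifiable.

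- *A journal article condenses the full protocol.* Removing devices at a visit is the sort of detail that may sit in an operating procedure, and its absence alone would be no finding. The point here is different: an unqualified property is asserted, a described design feature puts it at risk, and the only safeguard described does not meet that risk. If a masking step exists elsewhere, one clause closes the point.

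- *Little can be biased.* This largely stands. Digital instruments and numeric repeat rules leave little discretion for weight and blood pressure. A reader might take the repeat rules as giving the assessor wide latitude, or the 0.5 cm tolerance as the size of the possible bias; neither reading is right, for the reasons in the check. Waist circumference remains.

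- *No direction of bias is shown.* Also correct. Both arms receive the same app, and the Background calls the effect of automated monitoring on efficacy unknown, so there is no obvious arm for an assessor to favour. The Analysis section also commits only to selected secondary outcomes and does not name waist. This limits the consequence, but it does not make an unprotected blinding claim reliable.

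**Conclusion.** The point holds in a limited form. The plan declares the assessor blinded while giving one arm only a wrist-worn tracker after visit 2, and describes nothing that would stop the tracker from showing the arm at visits 4, 6 and 8. The article does not establish that blinding fails; it leaves a stated property at risk.

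This rests on two assumptions: that some device-arm participants attend with the tracker on, and that user-entered participants, who were not tracker users at entry, do not take one up during the 9 weeks. The proportion who would be unmasked is not known, and the size and direction of any resulting bias cannot be derived. The practical exposure is mainly waist circumference at three of four assessments. The primary comparison is not affected. It is worth correcting because the remedy costs almost nothing and an inaccurate blinding statement would carry through to the trial report.

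**What to change.** Instruct participants in both arms to remove all wrist devices before entering the measurement room at visits 4, 6 and 8, and not to tell the assessor how they monitor their behaviour. Giving the same instruction to both arms keeps it from being a signal in itself. It can go into the visit booking or reminder and the visit procedure, and needs no extra staff. If a step of this kind is already in place, state it next to the blinding claim.

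If it is not adopted, or if visits have already taken place without it, qualify the blinding statement for visits 4, 6 and 8 in both sections where it appears, and in the report.

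The downside is a short gap in tracker data for the device arm at three visits.

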### Intervention

“*Balanced*” is multi-behavioural intervention to increase time spent being physically active, decrease sedentary time and improve sleep quality. Intervention strategies include the provision of educational materials (e.g. health benefits of target behaviours, National guidelines on each behaviour, behaviour change strategies, creating action plans, sleep hygiene), goal setting and daily self-monitoring. Participants were not required to use the app for any specified time period however were instructed that it was designed for daily monitoring of behaviour and that they could use it as little or as much as they preferred. No prompts were provided to use or engage with the intervention. The intervention is able to be continuously accessed throughout the intervention and assessment periods and is accessible through a specifically designed mobile device app, available on both Android and iOS operating systems. The usability of the platform has been previously evaluated using a think aloud methodology similar to other research [43].

The development of the intervention platform was guided by operationalising constructs from social cognitive and self-regulatory theories (e.g., *education, goal setting, self-monitoring, feedback on behaviour)* which are consistently identified as important drivers of behaviour change [44–47]. The intervention platform has five sections as detailed below consistent to both intervention groups: 1) *Dashboard*, 2) *Your Stats* 3) *Progress*, 4) *Resources* and 5) *My Profile*.

